## **Plan of investigation**

*The study will consist of four parts.*

- 1) Retrospective multicentre cohort study regarding the incidence, risk factors, clinical phenotypes, microbiology and resistance, treatment, and outcome of children with iGAS in different European countries
- 2) Observational surveillance study regarding the incidence, risk factors, clinical phenotypes, microbiology and resistance, treatment, and outcome of children with iGAS in different European countries
- 3) Setting survey, regarding national and regional aspects of healthcare possibly impacting iGAS incidence and the care for children with iGAS.
- 4) A surveillance study that registers the increase of other invasive or emergent infectious diseases.

The complete study is a non-profit study.

**Research protocol: PEGASUS: Paediatric European Group A Streptococcal United Study.**

**Version 1.4. 09-07-2024.**

*Retrospective study:*

Participating centres will be asked to report all iGAS cases in the specified time period.

Anonymized data will be collected in an online database. Data will be combined into one dataset and then compared and analysed in combination and per country. Insights from the retrospective data collection phase will be used for the development and implementation of the surveillance part of the study.

*Surveillance study:*

An online database will be used that for all new iGAS cases. Data collection will take place retrospectively once a month. Reporting by the participating centres will take place once a month and reminders will be sent regularly.

The data will be published online on a monthly basis without information that can be traced back to individual patients. Online data will be displayed as numbers as well as visually.

*Setting survey:*

An online survey will be sent to the lead investigators of each participating centre to collect information on national and regional aspects of healthcare possibly impacting iGAS incidence and the care for children with iGAS, such as vaccination schedules and vaccination rates and primary care availability.

*Surveillance study for other invasive or emergent infectious diseases*

An online database will be used for other invasive or emergent infectious diseases. Data collection will take place retrospectively once a month. Reporting by the participating centres will take place once a month and reminders will be sent regularly.

The data will be published online on a monthly basis without information that can be traced back to individual patients. Online data will be displayed as numbers as well as visually.

**Inclusion criteria:**

- All children (1 month-18 years)
- attending the Emergency Department and/or admitted to the participating hospital - with iGAS infection or other invasive or emergent infectious disease.

**Time period**

- 1) January 2015 to April 2023\*
- 2) April 2023 – onwards

\* For the primary research questions, data collection will take place starting from 2018.

For the secondary research questions, data collection will take place from 2015 for those settings where this data is available and easily retrievable, for all other settings, data collection will take place from 2018.

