## **Index visit**

The visit in which the sample is taken that later shows proof of group A streptococcus or another invasive/emergent pathogen.

This is not known at the time of visit, as these results take time.

This does not have to be the first visit in the disease episode.

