## **Research protocol: PEGASUS: Paediatric European Group A Streptococcal United Study.**

**Version 1.4. 09-07-2024.**

as rounded age and time of visit will be collected as shift (day, evening, night), month and year of presentation to ensure patient data cannot be traced back to individual patients. To ensure data will remain truly anonymous, settings will be instructed to not store a local key that can link database data to local patient data.

In case of existing surveillance (UK, Switzerland), existing data will be exported anonymously and combined into a database containing data from all participating countries. Harmonization of data will take place to ensure the comparability and completeness of the collected data.

A survey per hospital will collect information on national and regional aspects of healthcare, such as vaccination schedules, vaccination rates, availability of primary care, funding of health care system, availability of rapid testing for group A streptococcal disease, and COVID NPI's.

After data collection, data will be stored and analyzed on a local secure hospital server of Noordwest Ziekenhuisgroep.

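### April 2023 falls in both study periods and no rule stops two participating hospitals from entering the same child; suspected duplicates can be flagged but not verified at source

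*Protocol*

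**What the plan says.** **Periods.** The Time period section gives part 1 as "January 2015 to April 2023" and part 2 as "April 2023 – onwards". It states neither a day nor whether the end month is included. A footnote adds: "For the primary research questions, data collection will take place starting from 2018".

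**Reporting.** Under Plan of investigation, the retrospective part states: "Participating centres will be asked to report all iGAS cases in the specified time period". The surveillance database is described as being "for all new iGAS cases. Data collection will take place retrospectively once a month".

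**Eligibility.** The inclusion criteria cover children with iGAS "attending the Emergency Department and/or admitted to the participating hospital". There is no limit of one record per episode, and nothing says which hospital reports a transferred child.

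**Index visit.** This is defined as "The visit in which the sample is taken that later shows proof of group A streptococcus" (or another invasive or emergent pathogen). The section adds that it need not be the first visit of the episode. It is not written as a rule for inclusion or counting.

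**Identifiers.** Under Data collection and online database, age is rounded and the visit is recorded by shift, month and year. In addition, "settings will be instructed to not store a local key that can link database data to local patient data". The variable list has gender, comorbidity, vaccination status, co-infection, diagnosis, microbiology, *emm* type, resistance, ICU admission and 30-day death, but no transfer item. Existing UK and Swiss surveillance data are to be merged in; harmonisation is mentioned, de-duplication is not.

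**The concern.** Two gaps let one episode become two records.

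The first is small. Read literally, a case from April 2023 belongs to both parts.

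The second matters more. A child seen in one participating emergency department and then admitted to another participating hospital meets the eligibility criterion at each, and both centres are asked to report all their cases. Children who are transferred are likely to be the sicker ones, so duplicates would not be a random sample of cases. They would raise the case count used for primary question 1. They would also raise the ICU and death proportions used for primary questions 2 and 3, and by different amounts in countries with different transfer patterns or different numbers of linked participating hospitals.

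This is a matter of data collection. An analysis plan can specify a matching algorithm, but it cannot supply a transfer status that was never recorded, nor send a query to a centre that holds no key.

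**Working it through.** The protocol states no transfer rate, duplicate rate or expected case count, so there is no figure of its own to reproduce. The rates and shares below are assumptions, shown as ranges.

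**1. The boundary month.** January 2018 to April 2023 inclusive is 5 × 12 + 4 = 64 months, so April 2023 is 1/64 = 1.6% of the period for the primary questions. From January 2015 it is 1/100 = 1.0%. In the worst case every April case is entered in both parts and the parts are pooled unchecked. With cases spread evenly over a post-NPI window of *m* months, the inflation is then 1/*m*:

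- *m* = 12: 8.3%
- *m* = 14: 7.1%
- *m* = 18: 5.6%

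The protocol does not fix the window length. Because month and year are recorded, assigning April to one part removes the overlap. That is safe only if each centre's April is complete in the part that is kept. If centres read the boundary differently, some April cases may sit only in the other part. A month split by day cannot be rebuilt, because day is not collected.

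**2. Effect of transfers on the ICU share.** Take 100 true cases with 30 in ICU (assumed), and let a fraction *f* of the ICU children be entered twice. The observed share is (30 + 30*f*)/(100 + 30*f*).

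| *f* | Records | ICU records | Observed ICU share | Count inflation |
|---|---|---|---|---|
| 0 | 100 | 30 | 30.0% | 0% |
| 10% | 103 | 33 | 32.0% | 3% |
| 25% | 107.5 | 37.5 | 34.9% | 7.5% |
| 50% | 115 | 45 | 39.1% | 15% |

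Two countries with the same true share of 30%, one with no double entry and one with *f* = 25%, would appear as 30% and 35%. The 30-day death proportion moves in the same direction if children who die are more often transferred and both hospitals record the death.

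**3. Effect on the incidence rate ratio.** With duplicate shares d₀ before and d₁ after, the spurious ratio is (1 + d₁)/(1 + d₀).

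- Constant share: 1.00, no bias
- 5% to 10%: 1.10/1.05 = 1.05
- 5% to 15%: 1.15/1.05 = 1.10
- 10% to 20%: 1.20/1.10 = 1.09

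**4. Can duplicates be flagged?** For *n* different children in one country and month, the expected number of chance matches is *n*(*n* − 1)/2 times the match probability. Assume uniform, independent categories: 18 ages, 2 genders, 5 diagnosis groups, 5 *emm* types.

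| Matching on | Probability | *n* = 5 | *n* = 10 | *n* = 50 |
|---|---|---|---|---|
| Age, gender | 1/36 | 0.28 | 1.25 | 34 |
| + diagnosis | 1/180 | 0.06 | 0.25 | 6.8 |
| + *emm* type | 1/900 | 0.01 | 0.05 | 1.4 |

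With small monthly counts and known *emm* type, a match is good evidence of a duplicate. With large counts or missing *emm* type it is not. True duplicates may also be missed, because shift, and sometimes month, can differ between the two visits. In neither case can the centre confirm the match.

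**The case against.** A reader might infer that duplicates can be neither found nor removed. The documents do not support that. The April overlap can largely be settled from the recorded month and year, the end date can be read as exclusive, and a case already reported in part 1 is not naturally a new case in part 2. A doubled April needs every centre to enter every case twice and the analyst to pool without looking. Probable transfer duplicates can be flagged from gender, diagnosis, microbiology and *emm* type. All of this stands.

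A reader might also infer that the before-and-after incidence comparison must be biased. It need not be: a constant duplicate share cancels from the ratio, and differences in hospital linkage between countries do not by themselves vary by period.

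The index-visit definition is a further defence. A child first sampled at the second hospital has one index visit, and using that as the counting rule would remove much of the problem. But the protocol does not say to use it so, and positive samples at two hospitals give two index visits.

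Finally, matching rules and sensitivity analyses commonly sit in an analysis plan or data-management plan, which is not shown. That holds for the analysis step. It does not hold for the reporting rule and the missing transfer field, which determine what is collected.

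**Conclusion.** The point holds in a limited form. The two periods share an undivided month, and no rule prevents two participating hospitals from entering the same episode. With rounded age, month-level dates, no transfer field and no local key, a suspected duplicate cannot be verified at source.

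The boundary month alone is a modest ambiguity. The weight rests on the missing one-record-per-episode rule together with the missing transfer field. The exposed quantities are absolute counts, the ICU and death proportions, and country comparisons where transfer reporting differs. The rate ratio between periods is exposed only if double entry became more or less common over time, for instance as linked hospitals joined.

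The true size is unknown. The rise from 30% to between 32% and 39% rests on an assumed ICU share, on assumed double entry of 10% to 50% of ICU children, and on none among the others. It shows how sensitive the proportions are and is not an estimate for this study.

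**What to change.** 1. Set a non-overlapping cut-off by month of index visit, for example part 1 to the end of March 2023 and part 2 from April 2023. Have centres confirm that their April 2023 cases are complete in the part that keeps them.
2. Count one record per disease episode, reported by the participating hospital of the index visit. Define that as the first participating hospital with a GAS-positive sample. If the positive sample came from a non-participating hospital, it is the first participating hospital to treat the child. Without this second clause the rule would lose eligible children who are transferred in after sampling elsewhere.
3. Add a yes/no field for transfer from or to another participating hospital, for new entries.
4. Report a sensitivity analysis that excludes transferred-in records. For records already entered, including the merged UK and Swiss exports, state a probable-duplicate matching rule and report results with and without the flagged records.

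**Cost.** One date, one rule and one form field, with anonymity unchanged. Centres must check transfer status before entry. The field cannot be back-filled for anonymised records already entered. The Timetable placed part 1 collection in 2023 Q2 and this version is dated July 2024, so much of the retrospective data may have to rely on matching alone.

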## **Introduction**

Since the COVID-19 pandemic and the implementation of non-pharmaceutical interventions (NPIs) to reduce the spread of SARS-CoV-2, a secondary effect has also been reported on the epidemiology of other viruses and bacterial infections. [Kruizinga 2021; Cohen trends 2022] At first, a decrease was seen in paediatric infectious diseases, followed by an off-season rebound with increased frequency of several common paediatric infectious diseases, such as bronchiolitis and gastroenteritis. [Cohen trends 2022]

In line with this, in 2022 several European countries as well as the United States, reported a rapid increase in children presenting with invasive group A streptococcal infections (iGAS). [van Kempen 2022; WHO; UK surveillance; Ladhani 2022] Many of those children had severe disease needing paediatric intensive care unit (PICU) admission or causing mortality. Furthermore, it was noted that many of these children had a preceding infection with influenza virus or varicella zoster virus (VZV). (1)

One hypothesis explaining the increase in iGAS is related to the various NPIs introduced between 2020 and early 2022, with the aim of containing the COVID-19 epidemic, and consequently resulting in an 'immunity gap' in children. (2)

Although this increase was seen in several European countries [WHO; van Kempen 2022; UK Surveillance; Ladhani 2022] this has not been reported in all European countries. Possible explanations for differences between countries include differences in COVID NPIs, differences in vaccination schedules for VZV and influenza, differences in circulating M protein genes (*emm* types) or underreporting due to the lack of a systematic surveillance system.

Importantly, detailed and systematic data collection on the clinical phenotypes is lacking, which is essential to better understand the current incidence, risk factors and outcome across European. However, given the rapid increase of iGAS cases, the increased case fatality rate described in a recent study in the Netherlands [van Kempen 2022] and the fact that it is a treatable disease when recognized early, prompt collection and dissemination of data are imperative.

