## **Research questions**

### *Primary research questions*

1. What is the incidence of iGAS in children before, during and after COVID NPIs in different European countries?
2. Is there a change in clinical phenotypes and outcome during these periods?
3. Are there differences in clinical phenotypes and outcome between European countries?

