### *Secondary research questions*

4. Is there a change in *emm* types and other virulence factors during these periods?
5. Are there differences in antimicrobial resistance between periods and between countries?
6. Can we identify risk factors for iGAS infection (e.g., preceding infections, age)?
7. Can we explain differences between countries (e.g., differences in vaccination strategies, NPIs or *emm* types)?
8. Can we use this research network for early alarming on other invasive and emergent infectious diseases in children?

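### The staggered 2015/2018 start for the secondary questions could produce an apparent change in emm type or resistance between periods, if the early-start settings differ from the rest

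*Protocol*

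**What the plan says.** The Time period section of the Protocol sets two start dates for the secondary questions. It says that "data collection will take place from 2015 for those settings where this data is available and easily retrievable", and that "for all other settings, data collection will take place from 2018". The primary questions have one start date: "For the primary research questions, data collection will take place starting from 2018".

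Two of the secondary questions compare periods. Question 4 asks "Is there a change in *emm* types and other virulence factors during these periods", and question 5 asks "Are there differences in antimicrobial resistance between periods and between countries". The periods are those of primary question 1, namely before, during and after COVID NPIs. The Introduction places the NPIs between 2020 and early 2022.

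On analysis, the Plan of investigation (Retrospective study) says "Data will be combined into one dataset and then compared and analysed in combination and per country". The Statistical analysis section names interrupted time-series models for change over time. It mentions no term for setting and no restriction to a constant set of settings.

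**The concern.** All of 2015-2017 falls before the NPIs. For questions 4 and 5, the pre-NPI period therefore combines three years from settings with retrievable records and roughly two further years from every setting. The during and after periods come from every setting. The mix of contributing settings thus changes along the same axis as the comparison of interest.

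This matters only if early-start settings differ from the others in emm mix or resistance. The Protocol treats such differences as possible: the Introduction lists "differences in circulating M protein genes" among candidate explanations for differences between countries, and question 5 asks whether resistance differs between countries. Analysis per country removes the between-country part. It does not help within a country whose hospitals have different start years.

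At stake is the answer to questions 4 and 5: a reported shift in emm type or resistance across the NPI periods could come partly or wholly from the start-date rule.

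**Working it through.** The Protocol states no prevalence, case volume or sample size, so there is no figure of its own to reproduce. The start years and approximate NPI dates come from the Protocol; all other inputs are assumptions.

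**Set-up.** Take the pre-NPI period as 2015-2019 (5 years) in early-start settings and 2018-2019 (2 years) elsewhere. Assume constant yearly cases per setting and no true change in any setting. Let *f* be the early-start settings' share of cases once all contribute, and *p*E and *p*O the prevalence in early-start and other settings.

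- Early-start share of pre-NPI cases: *s* = 5*f* / (5*f* + 2(1 − *f*))
- Pooled prevalence before: *s*·*p*E + (1 − *s*)·*p*O
- Pooled prevalence later: *f*·*p*E + (1 − *f*)·*p*O
- Spurious change: (*s* − *f*)(*p*O − *p*E)

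**Example, *f* = 0.3.** *s* = 1.5/(1.5 + 1.4) = 0.517. With 5% and 15%, before = 0.517 × 5 + 0.483 × 15 = 9.8% and later = 0.3 × 5 + 0.7 × 15 = 12.0%, a rise of 2.2 points.

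**Grid** (before → later, %; spurious change in points):

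| *f* | *s* | 5% vs 10% | 5% vs 15% | 10% vs 30% |
|---|---|---|---|---|
| 0.1 | 0.217 | 8.9 → 9.5 (0.6) | 12.8 → 14.0 (1.2) | 25.7 → 28.0 (2.3) |
| 0.2 | 0.385 | 8.1 → 9.0 (0.9) | 11.2 → 13.0 (1.8) | 22.3 → 26.0 (3.7) |
| 0.3 | 0.517 | 7.4 → 8.5 (1.1) | 9.8 → 12.0 (2.2) | 19.7 → 24.0 (4.3) |
| 0.5 | 0.714 | 6.4 → 7.5 (1.1) | 7.9 → 10.0 (2.1) | 15.7 → 20.0 (4.3) |
| 0.7 | 0.854 | 5.7 → 6.5 (0.8) | 6.5 → 8.0 (1.5) | 12.9 → 16.0 (3.1) |

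The range is 0.6 to 4.3 points. With *p*E = *p*O the change is 0 in every row. If early-start settings have the higher prevalence, the sign reverses.

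**Different cut date.** With NPIs taken to start at the end of March 2020, early-start settings have 63 pre-NPI months and the others 27. With half the cases in early-start settings, *s* = 63/90 = 0.70; resistance of 10% vs 4% then gives 0.70 × 10 + 0.30 × 4 = 8.2% before and 7.0% later, a difference of 1.2 points. With a quarter of the cases, *s* = 15.75/(15.75 + 20.25) = 0.4375; 20% vs 2% gives 9.9% before and 6.5% later. That second result needs a tenfold contrast between settings and is an extreme case.

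**Effect on a test.** At *f* = 0.3 with 500 cases per period, a two-sided 5% comparison of the two pooled proportions (normal approximation) would reject about 20% of the time (5% vs 15%) or 38% (10% vs 30%). With 1000 per period it would reject 34% or 65%.

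**Time series without a setting term.** The step in composition falls at January 2018, inside the pre-NPI segment, so it tilts the baseline trend. With *f* = 0.3 and 5% vs 15%, the yearly pooled values for 2015-2019 are 5, 5, 5, 12, 12. An unweighted straight line has mean 39/5 = 7.8 and slope (−2×5 − 1×5 + 0×5 + 1×12 + 2×12)/10 = 2.1 points per year. It projects 7.8 + 3 × 2.1 = 14.1% for 2020, against an actual 12%. The series would show a shortfall of 2.1 points where the crude comparison shows a rise.

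**After the fix.** With all settings starting in 2018, *s* = 2*f*/(2*f* + 2(1 − *f*)) = *f*, and the spurious change is 0 under the same assumptions.

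**The case against.** The strongest reply is that the Time period section is a collection rule. It does not say that 2015-2017 isolates go into one crude pre-NPI proportion. The choice of analysis set commonly sits in a statistical analysis plan, which is not shown here, and collecting extra early data prevents no valid analysis. Every setting contributes from 2018, so the problem is partial and removable. This much stands, and it is why the point concerns what could happen if the text is followed as written. It does not dispose of the point: the unequal window is fixed in the Protocol, which plans a combined analysis and says nothing on how the extra years may be used.

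A second reply is that the named method is interrupted time series, not a comparison of crude proportions. That is correct for change over time, but without a setting term the time series is exposed too, through its baseline trend.

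A third reply is that emm differences between countries appear only as a possible explanation, and resistance differences only as an open question. That is also correct: the documents do not establish that early-start settings differ, and they say nothing about differences between hospitals within a country.

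A reader might go further in two ways that the documents do not support. One is that an artefact in emm type or resistance would feed question 7 as an explanation of the surge. Question 7 asks about differences between countries, not change over time, and its examples do not include resistance. The other is that 2015-2017 cases are wrongly withheld from primary question 1. A single 2018 start for the primary questions is itself a common-window safeguard, and the Protocol does not promise complete 2015-2017 case counts from any setting.

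**Conclusion.** The concern holds in conditional form. As written, the start-date rule weights the pre-NPI period for questions 4 and 5 towards a self-selected subset of settings. In the combined analysis, and within any country whose hospitals start in different years, this could produce an apparent change in emm type or resistance when no setting has changed.

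The spurious change is zero if early-start settings resemble the others. On the assumed grid it is about 0.6 to 4.3 percentage points. These sizes rest on invented prevalences and case shares, constant case rates and no true change, so they show the order of magnitude and do not estimate what this study would see. It would be wrong to infer that the rule will produce a false shift, or that period and setting are fully confounded: about two pre-NPI years are common to all settings. The primary questions are unaffected.

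**What to change.** State in the Time period and Statistical analysis sections that:

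- between-period comparisons of emm type and resistance use the common window from 2018 in all settings;
- these comparisons are stratified by or adjusted for setting, or for country where setting is not recorded;
- 2015-2017 data are used only in a within-setting analysis limited to settings that supply the whole period.

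The second item is needed as well as the first. The increase was reported in some but not all countries, so even from 2018 the pooled case mix can shift as the affected countries contribute more cases. The variable list under Data collection does not name setting, though it may not be exhaustive, so confirm that setting is recorded for each case.

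The change takes a few sentences and no new data, provided setting is recorded. It costs a somewhat wider interval for the pre-NPI estimate, because the 2015-2017 isolates leave the pooled figure. A longer-baseline analysis for question 1 is at most an optional sensitivity analysis, in settings with complete 2015-2017 case counts.
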